## Abstract

**Background:**

Comorbid psychiatric disorders are frequent in children with intellectual disability (ID). Given the limitations of drugs treatments, cognitive remediation could be a promising tool to reduce these challenging behaviors but evidence is still scarce. Our group recently developed the «COGNITUS & MOI» program that is designed to train the attentional and visuospatial skills in children with ID. This study investigates the efficiency of the «COGNITUS & MOI» program in this condition.

**Methods:**

Children (age: 6.00–13.11) with mild to moderate ID and behavioral problems, will benefit from a therapy during a 16 week randomized controlled trial. One group will be randomly treated with the «COGNITUS & MOI» program and the other with a motor skill and video viewing intervention. All participants will undergo a behavioral, functional and neurocognitive assessment at baseline, post-intervention, and 6-month follow-up. Primary outcome will be the change from the baseline of the score on the “hyperactivity – noncompliance” subscale of the Aberrant Behavior Checklist.

**Discussion:**

If the results are conclusive, the «COGNITUS & MOI» program could be added to the therapeutic arsenal against challenging behavior in children with ID.

**Trial registration:**

ClinicalTrials NCT02797418. Date registered: 8th of June 2016.

## Background

Intellectual disability (ID) is a neurodevelopmental medical condition defined by poor cognitive functioning and adaptive skills. It includes a lack of autonomy in daily life and weak adaptation to the environment. Comorbid psychiatric disorders frequently occur with ID [1–3]. Unfortunately, pharmacological treatments are often poorly effective and/or generate side effects [4–6]. Non-drug treatments could therefore be of particular interest. Among these approaches, cognitive remediation aims at developing strategies to overcome the daily impact of cognitive deficits [7] and could be a promising tool to reduce challenging behaviors in children with ID. Indeed, specific cognitive profiles - especially memory, attentional, visuospatial and executive deficits - are well documented in children with ID [8–10]. Impairment of these functions has been related to psychiatric and more generally to behavioral problems in other medical conditions [11, 12]. Moreover, attentional and visuospatial skills must underlie social cognition abilities, especially facial emotion recognition [13]. Impairment of social cognition frequently occurs in ID [14–16] and is associated with challenging behaviors [16, 17]. The stimulating idea that comes out of these results is that appropriate cognitive training would allow an improvement in environmental stimuli processing and consequently in the behavioral response of children with ID.

Despite these converging data, evidence-based non-drug treatments for behavioral problems in ID are still lacking. Previous studies have shown that cognitive remediation could improve cognitive abilities in children with ID [18–22] but - to our knowledge - few were interested in behavior and adaptive skills in daily life [23, 24].

Our group recently developed the «COGNITUS & MOI» program, a cognitive remediation tool designed to train the attentional and visuospatial skills of 5–13 year-old children. COGNITUS is a friendly cartoon character that accompanies the child throughout various activities in paper-and-pencil, computerized, and at-home formats [25]. The «COGNITUS & MOI» program could be of particular interest concerning challenging behaviors in children with ID for several reasons. First, the program is based on an active coaching approach and a flexible set of exercises that can be individually adapted according to the child’s clinical profile. This is especially suitable in ID because of the high heterogeneity of clinical presentation. Second, this program focuses on visuospatial and attentional skills that could be closely related to behavioral disturbances. Therefore, the focus of this randomized controlled study is the «COGNITUS & MOI» program in children with mild to moderate ID.

### Objectives of the study

The primary objective of this study is to evaluate the effectiveness of the «COGNITUS & MOI» program compared to a motor skill and video viewing intervention in terms of children’s behavioral problems.

The secondary objectives are as follows:to investigate the effectiveness of the «COGNITUS & MOI» program compared to a motor skill and video viewing intervention on children’s neurocognitive abilities;to investigate the effectiveness of the «COGNITUS & MOI» program compared to a motor skill and video viewing intervention on functional outcomes in children (adaptive behaviors, quality of life and self-esteem); andto evaluate the long-term maintenance (6 months after) of the beneficial effects of these treatments.

It is hypothesized that children who undergo the «COGNITUS & MOI» program will demonstrate greater and more sustainable improvements in behavioral problems, neurocognitive abilities and functional outcomes than those who receive a motor skill and video viewing intervention.

## Methods and design

### Design

Two groups of 100 children will benefit from a therapy during a 16 week randomized controlled trial. One group will be randomly treated with the «COGNITUS & MOI» program and the other with a motor skill and video viewing intervention. In both groups, the preliminary session will consist of the presentation of the program to the child and their parents by the therapist. The following 16 therapy sessions will occur once a week and include paper-and-pencil, computer-based and at-home activities. All participants will undergo a behavioral, functional and neurocognitive assessment by an experienced psychologist. The assessment will occur before, immediately after and 6 months after the end of the program (baseline, post-treatment and 6-month follow-up). Figure 1 shows a schematic overview of the design of the study.

**Fig. 1 Fig1:**
[figure not shown]
Schematic overview of the «COGNITUS & MOI» study protocol

### Inclusion and exclusion criteria

Children from 6 to 13 years old with mild to moderate intellectual disability in line with DSM-V criteria and behavioral problems are eligible for this study. Detailed inclusion and exclusion criteria are summarized in Table 1. Pychotropic medications and occupational, speech, orthoptic and/or psychomotor therapies should remain unchanged thorough the protocol. The intervention will be discontinued in case of clinical aggravation, patient’s refusal to continue or after more than two unjustified absence rated by therapist.

**Table 1 Tab1:** Inclusion and exclusion criteria

Inclusion criteria	Exclusion criteria
• age between 6 years 0 month and 13 years 11 months • ABC scale total score equal or higher than 15 • total IQ score between 45 and 70 (WPPSI-III, WPPSI-IV, WISC-IV or WISC-V scale) AND standard score of at least one domain of the VABS-II between 40 and 70 AND measurements carried out for less than 18 months • French speaker • Psychotropic medication remained unchanged for 1 month • Occupational, speech, orthoptic and/or psychomotor therapies remained unchanged for 1 month	• DSM-5 criteria for autism spectrum disorder • vascular, infectious or degenerative neurological condition • medication for somatic problem that might interfere with brain functioning

*WPPSI* Wechsler Preschool and Primary Scale of Intelligence (Wechsler, 2004; 2014), *WISC* Wechsler Intelligence Scale for Children (Wechsler, 2005; 2016), *ABC* Aberrant Behavior Checklist (Aman & Singh, 1986), *VABS-II* Vineland Adaptive Behavior Scales – Second Edition (Sparrow, Cicchetti, & Balla, 2015)

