### Assessments and outcomes

Assessments will include behavioral problems, neurocognitive abilities (language, memory, praxis and visuospatial abilities and attentional and executive functions), social cognitive processes (emotion recognition and theory of mind abilities) and functional outcome (quality of life, self-esteem and adaptive and daily living skills) measures. Assessments will involve the child, their parents and an experienced psychologist.

The primary outcome is the change from the baseline of the score on the “hyperactivity – noncompliance” subscale of the Aberrant Behavior Checklist [26].

Secondary outcomes are as follows:the change from the baseline of the scores for a semi-structured interview investigating adaptive behaviors and daily living skills,the change from the baseline of the scores of two questionnaires investigating quality of life and self-esteem,the change from the baseline of scores of paper-and-pencil subtests, computerized subtests and questionnaires investigating praxis and visuospatial functions, memory, language, attentional and executive functions, and social cognition, andthe change of all scores from post-treatment to the 6-month follow up.

See Table 2 for a detailed overview of the assessments and outcome measures.

**Table 2 Tab2:** Measurements

	Kind of measure	Name	type	informant	recruitment	baseline assessment	post-treatment assessment	6-months follow up assessment
	IQ estimation	WPPSI-III, WPPSI-IV, WISC-IV or WISC-V	P&P	C	*			
*primary outcome*	behavioural problems	ABC	Q	P	*	*	*	*
*secondary outcome*	adaptive and daily living skills	VABS-II	S Int.	P	*	*	*	*
	quality of life	KIDSCREEN-27	Q	P		*	*	*
	self esteem	self-esteem subscale MDI-C	Q	C		*	*	*
	lexical knowledge	PPVT	P&P	C		*	*	*
	learning and long term memory	word list CMS	P&P	C		*	*	*
		dot locations CMS	P&P	C		*	*	*
	praxis and visuospatial functions	visuomotor precision NEPSY-II	P&P	C		*	*	*
		imitating hand positions NEPSY-II	P&P	C		*	*	*
		arrows NEPSY-II	P&P	C		*	*	*
		block construction NEPSY-II	P&P	C		*	*	*
		route finding NEPSY-II	P&P	C		*	*	*
	attentional functions	sky search TEA-Ch	P&P	C		*	*	*
		alertness TAP 2.3	CT	C		*	*	*
		auditory attention NEPSY-II	P&P	C		*	*	*
		divided attention TAP 2.3	CT	C		*	*	*
	executive functions	Go/NoGo TAP 2.3	CT	C		*	*	*
		response set NEPSY-II	P&P	C		*	*	*
		inhibition NEPSY-II	P&P	C		*	*	*
		mazes WISC-III	P&P	C		*	*	*
	social cognition	affect recognition NEPSY-II	P&P	C		*	*	*

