### Sample size

To our knowledge, only one previous study has evaluated the effectiveness of a non-drug treatment using the “hyperactivity – noncompliance” score of the ABC as the primary outcome measurement [27]. A decrease of 3 points after treatment was found to be significant (M = 12.1; SD = 8.9 versus M = 9; SD = 7.4). Therefore, we hypothesize that following the motor skills and video viewing intervention, we will observe a 3 point decrease of the “hyperactivity – noncompliance” score. We expect that the decrease will be double for the «COGNITUS & MOI» program: the difference between the two treatments would be at least 3 points. With an expected SD of 5, a power of 90%, 1:1 allocation into the two groups, two-sided testing and a significance level of 5%, a total sample of 126 participants is required. Given the insufficient information from the literature and the risk of dropout, 200 participants will be enrolled in the present study.

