### Statistical analysis

Descriptive statistics will be reported for each variable of interest for the two groups.

First, independent-sample t-tests or non-parametric Mann-Whitney tests will be run to assess the lack of differences between groups in age, IQ or severity of ABC scores at baseline (*p* < 0.05, two-sided).

Second, independent-sample t-tests or non-parametric Mann-Whitney tests will be run to compare the “hyperactivity – noncompliance” score change from the baseline to post-treatment assessment in the two groups (*p* < 0.05, two-sided).

Third, similar tests will be run for each secondary outcome measure. The score changes will be separately considered from the baseline to post-treatment assessment and from the post-treatment to 6-month follow-up assessment (*p* < 0.05, two-sided).

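### Children who stop the intervention early need a fixed assessment time, and the unadjusted change-score test should give way to a model using baseline, strata and both follow-up scores

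*Protocol article*

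**What the plan says.** All references are to the protocol article.

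- **Stopping** (Inclusion and exclusion criteria): "The intervention will be discontinued in case of clinical aggravation", and likewise if the patient refuses to go on or has more than two absences that the therapist rates as unjustified. The sentence concerns the intervention. It does not mention withdrawal from assessment.
- **Who is assessed, and when** (Design): "All participants will undergo a behavioral, functional and neurocognitive assessment by an experienced psychologist", and "The assessment will occur before, immediately after and 6 months after the end of the program".
- **Primary outcome** (Assessments and outcomes): "The primary outcome is the change from the baseline of the score on the “hyperactivity – noncompliance” subscale of the Aberrant Behavior Checklist". Table 2 lists it as a parent questionnaire collected at baseline, post-treatment and 6 months.
- **Primary test** (Statistical analysis): "independent-sample t-tests or non-parametric Mann-Whitney tests will be run to compare the “hyperactivity – noncompliance” score change" between baseline and post-treatment. Secondary outcomes get similar tests, with the post-treatment to 6-month change taken separately.
- **Expected loss** (Sample size): "Given the insufficient information from the literature and the risk of dropout, 200 participants will be enrolled", against a stated requirement of 126. No dropout rate is given.
- **Strata** (Randomization): allocation is stratified by two age bands and two IQ bands. The stated test uses neither the strata nor, beyond the subtraction, the baseline score.

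**The concern.** Children enter this trial because of behavioural problems, and the primary outcome is a behaviour score. Clinical aggravation, and to a lesser degree refusal and absence, can plausibly track that score. The therapist who rates absences is given the allocation, and parents know it too. One arm receives individual goals and coaching, the other fixed activities and passive videos. Control families are told the program may be available to them at the end of the study. Stopping could therefore differ between arms.

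Two things then matter. First, for a child who stops at, say, week 5, the end of the program could mean week 5 or week 16. Even with complete data, stopped children might be measured at a different time from the rest, and the 6-month visit inherits the same ambiguity. Second, a child with no post-treatment score contributes nothing to a t-test or Mann-Whitney test on change unless a value is imputed. If such children had mostly worsened, and more of them were lost in one arm, the comparison would be biased. Enrolling more children restores precision but does not remove bias of that kind.

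**Working it through.** **1. The plan's own figure.** Inputs from Sample size: difference 3, SD 5, power 90%, two-sided 5%, 1:1 allocation.

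- The normal approximation gives 59 per arm, 118 in total.
- The exact t-test gives 59.35, so 60 per arm, 120 in total.
- Dividing by the Mann-Whitney relative efficiency: 59.35 / 0.955 = 62.15, so 63 per arm, **126 in total**.

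The stated 126 is therefore reproduced by the Mann-Whitney variant and is conservative for the t-test. It is not in error.

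**2. Room for loss.** 1 − 126/200 = 0.37. T-test power is 0.988 with 200 children and 0.916 with 126. This concerns precision only.

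**3. Shift in one arm's mean when its worst-changing fraction q is missing.** For normally distributed change with SD 5, where a higher score is worse, the observed mean falls (looks better) by 5·φ(z)/(1 − q), with z the upper-q normal quantile. The values of q are assumptions; the document gives none.

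| q | shift (points) |
|---|---|
| 5% | 0.54 |
| 10% | 0.97 |
| 15% | 1.37 |

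Shift in the between-arm difference:

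- 10% against 5%: 0.97 − 0.54 = **0.43** (0.43/3 = 14% of the target).
- 15% against 5%: 1.37 − 0.54 = **0.83** (0.83/3 = 28% of the target).

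**4. Direction.** Simulation with 5,000 runs, 100 children per arm, SD 5 and a t-test on children with both scores. Worsening means a change above 0. Mean change is −3 in control, and −3 (no effect) or −6 (planned effect) in the program arm.

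| True difference | Worseners lost: program / control | Mean estimate | Significant |
|---|---|---|---|
| 0 | 50% / 50% | about 0 | 5% |
| 0 | 50% / 25% | −0.5 | 11% |
| 0 | 50% / 0% | −1.0 | 27% |
| −3 | none lost | −3.0 | 99% |
| −3 | 50% / 50% | −2.5 | 96% |
| −3 | 100% / 100% | −1.8 | 83% |

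With no true effect, equal loss rates give no bias. Heavier loss in the program arm gives a false benefit. When the program works, the same rule in both arms shrinks the estimate, because control has more worseners to lose. If stopped children are all assessed at the scheduled time, the bias from missing scores is zero.

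**5. The test itself.** With equal variance at both visits and correlation ρ between them, change has variance 2σ²(1 − ρ) and a baseline-adjusted comparison has σ²(1 − ρ²). The ratio of the second to the first is (1 + ρ)/2, which is below 1 for any ρ below 1. Adjustment for baseline is therefore at least as precise as the change score, and the data needed are already collected. Adding the 6-month score lets a child with only that follow-up contribute.

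**The case against.** A reader might infer that worsening children are dropped from the primary result and that this favours the program. The document does not support that. The stopping sentence ends the intervention, not follow-up. The Design section says all participants are assessed. No sentence states a complete-case analysis, and either named test can be run on imputed data. A false benefit requires heavier loss in the program arm; other patterns give no bias or pull the estimate towards no difference.

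The absence of an analysis set or a missing-data rule is not a fault here, since a condensed article commonly leaves these to the full protocol or analysis plan. Nor should the 37% be read as planned dropout: the increase to 200 is attributed first to thin literature and then to dropout.

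On timing, 16 weekly sessions make the scheduled end the natural reading, and Figure 1, which was not available for this review, may settle it. The loss rates used above are hypothetical, and aggravation is not defined by the hyperactivity subscale, so lost children need not come from its worst tail. Stops and their reasons can also be tabulated by arm, so the problem would not be invisible.

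Finally, a mixed model assumes data missing at random, and with baseline as a covariate a child with neither follow-up score adds no outcome data. It does not cure loss caused by unobserved worsening.

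All of this stands. What remains is that the timing wording is ambiguous for early stoppers, and that the stated test makes less use of the collected data than an available alternative.

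**Conclusion.** The point holds as a risk and as a case for a better-specified analysis, not as a demonstrated bias. Stopping may be related to the outcome, the assessment time is ambiguous for children who stop early, dropout is expected, and the primary test uses only children with both scores unless values are imputed. Under assumed losses of the worst-changing 10% to 15% in one arm against 5% in the other, the difference moves by 0.43 to 0.83 points of the 3-point target. This rests on SD 5, normally distributed change and losses confined to the worst tail. Actual size and direction are unknown. The required sample of 126 is sound. Independently of missing data, a model adjusted for baseline and strata that also uses the 6-month score is preferable to the unadjusted change-score test.

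**What to change.** 1. State that every randomised child has the post-treatment and 6-month assessments at times counted from randomisation or from the planned program end, whether or not the intervention was stopped, and is analysed in the arm assigned.
2. Replace the unadjusted test on change with a model of the post-treatment and 6-month scores, with arm-by-visit terms, baseline score and the age and IQ strata. The primary result is the arm difference at post-treatment. This gains precision and uses children who have either follow-up score.
3. Because that model assumes data missing at random, add one sensitivity analysis that assigns worse scores to children who stopped for aggravation and have no score.

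The cost is slightly more analysis work, and obtaining a parent questionnaire from families who stopped. Nothing in this changes when the intervention is stopped.

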### Recruitment

Recruitment will occur among 6 French clinical genetic, psychiatric, or neurologic departments of public hospitals. Detailed oral and written information about the study will be given to the child and their parents by the investigator. For ethical reasons, parents will be informed that children allocated to the motor skill and video viewing intervention could benefit from the «COGNITUS & MOI» program at the end of the study. Inclusion and exclusion criteria will be carefully verified by medical investigators. Parents will give written informed consent, and children will provide oral consent before inclusion in the research program.

### Randomization

Four strata will be constructed based on age (6–9 and 10–13 years) and total Intellectual Quotient (IQ) score (45–55 and 56–70) to balance characteristics between the treatment groups. After the inclusion of a child, randomization will be done by the statistician involved in the research project and provided to each therapist. The participants and their parents will rate several measures – including primary outcome measures – and will be informed of their group assignment. However, the psychologist will blindly assess the participant’s behavior, cognitive abilities and functional outcomes at baseline, post-treatment, and the 6-month follow-up.

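### Centre enters neither the randomisation nor the primary analysis, and the analysis also leaves out the age and IQ strata: a modest loss of precision, not a bias

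*Protocol article*

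**What the plan says.** - **Allocation** (Randomization): "Four strata will be constructed based on age (6–9 and 10–13 years) and total Intellectual Quotient (IQ) score (45–55 and 56–70". The stated purpose is balance of characteristics between the groups. On who allocates, the section says that "randomization will be done by the statistician involved in the research project and provided to each therapist", after inclusion of the child.
- **Centres** (Recruitment): "Recruitment will occur among 6 French clinical genetic, psychiatric, or neurologic departments of public hospitals". The article gives no expected numbers per department.
- **Primary analysis** (Statistical analysis): "independent-sample t-tests or non-parametric Mann-Whitney tests will be run to compare the “hyperactivity – noncompliance” score change" from baseline to post-treatment. No centre, age or IQ term is named.
- **Baseline check** (Statistical analysis): tests are run "to assess the lack of differences between groups in age, IQ or severity of ABC scores at baseline". Centre is not in the list.
- **Target** (Sample size): the plan expects that "the difference between the two treatments would be at least 3 points". It assumes a standard deviation of 5 and aims for 90% power in two equal arms, which leads to a requirement of 126 children at the two-sided 5% level. Enrolment is then set at 200.

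**The concern.** Departments of genetics, psychiatry and neurology may see children whose behaviour changes differently over 16 weeks. If so, department predicts the outcome. Nothing in the stated allocation keeps the arms balanced within a department, and nothing in the stated analysis removes the effect of an imbalance. Part of any difference between departments then enters the treatment comparison as noise.

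The article fixes these points and does not leave them open: four strata made from two factors leave no room for a third, and the primary test is named. At stake are the precision of the primary estimate and the match between analysis and design. An unadjusted test also gives up whatever the age and IQ strata could explain.

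**Working it through.** **1. The plan's own sample size.** Inputs: difference 3, SD 5, power 90%, two-sided 5%, 1:1.
- The normal approximation gives 59 per arm, 118 in total.
- The exact t-test calculation gives 59.35, so 60 per arm, 120 in total.
- Dividing by the Mann-Whitney efficiency, 59.35 / 0.955 = 62.2, so 63 per arm, **126** in total.

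The stated figure is reproduced if the Mann-Whitney allowance was used; the article does not say so. By t-test, power is 91.6% at 126 and 98.8% at 200.

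**2. Size of the chance shift.** Assumptions, none of them in the article: allocation independent of centre, within-centre SD 5, and between-centre SD of the change score *s* = 1, 2 or 3. As a share of total variance, s²/(25 + s²), these are 4%, 14% and 26%, so *s* = 3 is a large centre effect.

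With N children and centre shares w, the SD of the centre-caused shift in the treatment difference is about s × √[(4/N)(1 − Σw²)].
- Six equal centres, N = 200: √(0.02 × 5/6) = 0.129, so 0.129 × s.
- Centre sizes 80/40/30/20/20/10: Σw² = 0.245, and √(0.02 × 0.755) = 0.123, so 0.123 × s.

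A simulation (2,500 runs per scenario, blocks of 4 within the age-by-IQ strata) agrees with the formula:

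| s | 1.96 × 0.129 × s | Simulated 95th percentile of shift |
|---|---|---|
| 1 | 0.25 | 0.25–0.27 |
| 2 | 0.51 | about 0.52 |
| 3 | 0.76 | 0.75–0.80 |

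**3. Bias and type I error.** Across the same runs the mean estimate was 3.0 in size when the true difference was 3, and 0.0 when it was 0. Type I error of the unadjusted t-test was 4.5–5.5%.

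**4. Precision and power at 200.** Without a centre effect the standard error is √(100/200) = 0.707. At s = 3, unadjusted, it is √(0.5 + 0.387²) = 0.806. Simulated power of the unadjusted test is 98–99% for s = 0 to 2 and about 96% for s = 3. With centre in the model it is about 98.5% at s = 3, even though allocation is not stratified by centre.

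**5. Power if only 126 children remain.** The multiplier becomes √[(4/126)(5/6)] = 0.163, so the 95th-percentile shift is 1.96 × 0.163 × s, or 0.32, 0.64 and 0.96 points. At s = 3 the unadjusted standard error is √(100/126 + 0.488²) = 1.016 and power is about 83%. Adjusting for centre keeps it at about 91%.

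**6. Balancing on centre without adjusting.** With centre-stratified blocks the 95th-percentile shift falls to 0.07–0.15 points for s = 2 and 3. The unadjusted t-test then has a type I error of only 2.8–3.9%, because its standard error still contains the centre variance that the design has removed. The adjusted model stays close to 5%.

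**7. How lopsided a department may become.** Assume 33 children per department, each allocated with probability 0.5. A 13:20 split or worse has probability 0.296 at one site and 1 − (1 − 0.296)⁶ = 0.88 at one or more of six. A split of 8:25 or worse has probability 0.0046 at one site and 1 − (1 − 0.0046)⁶ = 0.027 at any of six.

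**The case against.** **The design choice is legitimate.** Stratifying on prognostic factors and leaving centre out is common, and the design does what it says for age and IQ. Nothing in the article contradicts itself here. This stands, and it keeps the point minor.

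**The harm is small.** There is no average bias, and 200 children against 126 required leaves ample power. The eligibility criteria narrow the case mix (IQ range, minimum ABC score, autism excluded, stable medication and therapies). Using change from baseline removes stable differences in level between departments, though not differences in response. All of this stands. The between-centre SDs are assumptions and the true value may be near zero.

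**A stronger reading to avoid.** A reader might infer that a department could end up mostly in one arm, so that centre and treatment are confounded. The arithmetic does not support this. Moderate splits such as 13:20 are likely somewhere, but 8:25 at any of six equal sites has a chance of about 2.7%. A reader might also infer that therapy is delivered at each recruiting department, so that local therapist style travels with the centre. The article says where children are recruited, not where therapy takes place.

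What remains is that a factor which may predict outcome is ignored at both steps, and that the factors used to stratify are left out of the analysis.

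**Conclusion.** The point holds as a minor one about efficiency. As written, centre is accounted for in neither allocation nor analysis, and the analysis does not use age group or IQ group. The consequence is chance imbalance and lost precision, with no systematic bias and no type I error inflation. At 200 children the shift is unlikely to exceed about 0.25, 0.5 or 0.8 points for between-centre SDs of 1, 2 or 3, and power stays at about 96% or above. The cost grows if dropout is heavy: at 126 children and SD 3, power would be about 83% unadjusted.

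These sizes rest on assumed between-centre SDs, centre sizes and block size, and on reading the stated SD of 5 as the within-centre SD. No size can be put on the omission of age and IQ group, because the article does not say how strongly they predict change.

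**What to change.** **In all cases:** replace the unadjusted primary test with a linear model of the change in the ABC hyperactivity-noncompliance score from baseline to post-treatment, containing treatment, centre, age group and IQ group. The target difference is unchanged. Against the t-test the model uses seven more degrees of freedom (five for centre, one each for age and IQ group), which is negligible with 200 children. It needs one changed sentence in the Statistical analysis section, settled before outcome data are compared by arm.

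**If enrolment has not started:** also add centre to the allocation, for example by minimisation with a random element on centre, age group and IQ group. Crossing six centres with four strata would give 24 cells of about 8 children (200/24), which is why minimisation suits better than full stratification. The statistician already allocates each child after inclusion, so no extra children are needed. This must go together with the adjusted model, because balancing on centre while keeping an unadjusted test makes that test conservative.

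**Cost:** a slightly more complex analysis and allocation routine, and somewhat more predictable assignments in small centres unless the random element is kept. Predictability matters here because therapists and parents know the allocations.
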